# Effect of virtual reality combined with repetitive transcranial magnetic stimulation on musculoskeletal pain and motor development in children with spastic cerebral palsy: a protocol for a randomized controlled clinical trial

**DOI:** 10.1186/s12883-023-03359-4

**Published:** 2023-09-26

**Keywords:** Cerebral palsy, Virtual reality, Pain, Repetitive transcranial magnetic stimulation, Randomized Controlled Trial, Protocol

## Abstract

**Purpose:**

This trial aims to investigate the efficacy and safety of virtual reality (VR) combined with repetitive transcranial magnetic stimulation (rTMS) for improving musculoskeletal pain and motor development in children with unilateral spastic cerebral palsy (CP).

**Methods:**

This study protocol is for a randomized controlled trial consisting of 2 treatment sessions (3 days/week for 4 weeks in each session, with a 1-week interval between sessions). We will recruit children aged 3–10 years with unilateral spastic CP (Gross Motor Function Classification System level I or II). Participants will be randomly divided into 3 groups: the VR + rTMS group (immersive VR intervention, rTMS and routine rehabilitation therapy), rTMS group (rTMS and routine rehabilitation therapy), and control group (sham rTMS and routine rehabilitation therapy). VR therapy will involve a daily 40-minute movement training session in a fully immersive environment. rTMS will be applied at 1 Hz over the primary motor cortex for 20 min on the contralateral side. The stimulation intensity will be set at 90% of the resting motor threshold, with 1200 pulses applied. A daily 60-minute routine rehabilitation therapy session including motor training and training in activities of daily living will be administered to all participants. The primary outcome will be pain intensity, assessed by the Revised Face, Legs, Activity, Cry, and Consolability Scale (R-FLACC). The secondary outcomes will include motor development, evaluated by the 66-item version of the Gross Motor Function Measure (GMFM-66) and Fine Motor Function Measure (FMFM); balance capacity, measured by the interactive balance system; activities of daily living; and quality of life, measured by the Barthel index and the Chinese version of the Cerebral Palsy Quality of Life scale for Children (C-CP QOL-Child). Safety will be monitored, and adverse events will be recorded during and after treatment.

**Discussion:**

Combined application of VR therapy and rTMS may reveal additive effects on pain management and motor development in children with spastic CP, but further high-quality research is needed. The results of this trial may indicate whether VR therapy combined with rTMS achieves a better analgesic effect and improves the motor development of children with spastic CP.

**Trial registration:**

Registration number: ChiCTR230069853. Trial registration date: 28 March 2023. Prospectively registered.

## Introduction

Cerebral palsy (CP) is “a disorder of movement and posture due to a defect or lesion of the immature brain” [1, 2]. Pain is one of the most cited musculoskeletal disorders in spastic CP children, with a prevalence of up to 74% [3, 4]. It is an urgent issue in spastic CP, as pain may trigger physical and emotional complications, such as decreased mobility and irritability [5]. Chronic pain in children with spastic CP remains consistent (45%) or worsens (34%) between clinical visits and is considered strongly associated with reduced quality of life, as it may impact exercise and social participation, leading to developmental delay of motor and language function, as well imposing an enormous personal and economic burden [6].

Chronic primary pain is associated with injury to the thalamus or spinothalamic tract [7]. Primary pain from a musculoskeletal origin has rarely been reported [8]. Secondary pain caused by muscle spasms, postural asymmetries, and osteoarthrosis complications is highly prevalent in spastic CP. Muscle spasms lead to vessel compression and ischaemia, which activate local pain receptors [9]. Soft tissue may be under long-term compression due to postural asymmetries, and the resulting chronic pain occurs mostly in the back [10]. However, the identification of pain is often difficult for children who experience pain because children with spastic CP may not accurately express pain due to cognitive limitations [11]. Numerous previous studies have suggested that physical and occupational therapy may be basic treatments for pain control, including music therapy [12], games [13], and deep breathing training [14]. However, in a substantial proportion of CP patients, pain remains refractory and requires further therapy [3]. To date, analgesic-based treatments have focused only on pain and physical symptoms, neglecting overall function, especially balance function and activities of daily living.

Despite the acceptability of VR in children and the sustained effects of rTMS, it is currently unknown whether there is a synergistic effect of the combination of VR therapy and rTMS on pain in children with spastic CP. This study protocol combined VR therapy and rTMS with the aim of exploring the efficacy and safety of this combined treatment in improving the pain and motor development of children with spastic CP. We hypothesize that rTMS can improve pain in children with CP and that the combination of VR therapy and rTMS will show better efficacy than rTMS alone.

## Methods

### Study design

This is a randomized, single-blind (evaluator), prospective clinical trial (protocol version 2.0, date: 2023.02.28). Participants will be randomly and equally divided into 3 groups: the VR + rTMS group, the rTMS group, and the control group. Two 4-week sessions of treatment will be provided to participants, separated by an interval of one week. Assessments will be performed at baseline (week 0) and after the intervention (week 9). This study will follow the Standard Protocol Items: Recommendations for Intervention Trials (SPIRIT) guidelines [32] (Fig. 1) and the Consolidated Standards of Reporting Trials (CONSORT) statement (http://www.consort-statement.org (Fig. 2) [33]. The study’s trial registration number is ChiCTR230069853.

**Fig. 1 Fig1:**
[figure not shown]
SPIRIT checklist. FLACC, Face, Legs, Activity, Cry, and Consolability Scale; GMFM-66, 66-item version of the Gross Motor Function Measure; FMFM, Fine Motor Function Measure; C-CPQOL-Child, Chinese version of the Cerebral Palsy Quality of Life scale for children; PedsQL-CP, Pediatric Quality of Life Inventory Measurement Model: Cerebral Palsy Module

**Fig. 2 Fig2:**
[figure not shown]
CONSORT flowchart. GMFCS, Gross Motor Function Classification System; VR, virtual reality; rTMS, repetitive transcranial magnetic stimulation

### Ethics

The procedures in this protocol are in accordance with the standards of the Declaration of Helsinki [34]. The trial will adhere to the study protocol. The private and personally identifiable information of the participants will be strictly protected. This study has been approved by the Xinhua Hospital Ethics Committee (Shanghai, China) [XHEC-C-2023-006-2]. Two sets of comparisons will be conducted (the VR + rTMS group vs. the rTMS group and the rTMS group vs. the control group). Considering a potential dropout rate of 15%, a total of 108 children (36 in each group) will be enrolled. Written informed consent to participate will be obtained from all study participants and in case of minor’s informed consent will be obtained from parents/legal guardian(s) before the children are randomly assigned to groups and can choose the desired treatments after the trial.

### Study population, recruitment, and eligibility criteria

Assessment will be undertaken by the same physiotherapy team experienced in the management of paediatric patients. All assessors involved in data collection will be trained in the study procedures and familiarized with the use of the study instruments and measurements. Participants will volunteer to participate through the outpatient service of the Rehabilitation Medicine Department, Xinhua Hospital, School of Medicine, Shanghai Jiaotong University. Children who are diagnosed with CP by an experienced paediatrician based on the Chinese Rehabilitation Guidelines for Cerebral Palsy (2022) [35] will be included. Another trained paediatrician will provide information about this study both verbally and in writing to children who meet the eligibility criteria. Children and their guardians will be informed that they will be randomly assigned to one of three effective treatments to determine which treatment best improves pain and development. After enrolment, an independent researcher will implement random assignment by telephone to avoid predictability. Basic information (age, sex, height, weight) and function classification with the Gross Motor Function Classification System (GMFCS) will be collected [36].

#### Inclusion criteria

①Diagnosis of spastic CP,②Aged 3 to 10 years,③GMFCS level I or II,④A history of pain reported by participants or their guardians.

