#### VR + rTMS group

Participants in the VR + rTMS group will receive VR therapy, rTMS, and routine rehabilitation. The interventions will be conducted in the following order: routine rehabilitation, VR therapy, and rTMS.

The virtual reality rehabilitation system (VRRS, Khymeia Group, Noventa Padovana, Italy) will be used to administer VR therapy. Each participant will be fully immersed in the virtual environment that can provide visual and acoustic feedback. Participants will be guided to perform active motions such as touching or grasping specific objects, balance control, lower limb movement, and hip flexion in specific situations for 40 min [38]. Before the start, therapists will adjust the difficulty and intensity according to the child’s motor function and responses to VR.

rTMS will be administered through a figure-eight coil connected to a Yiruide NS1000 stimulator (Yiruide Company Limited, Wuhan, China). The resting motor threshold (rMT) is defined as the stimulation intensity that induces a motor evoked potential of the contralateral abductor pollicis brevis that reaches 50 µV more than 5 times in 10 stimulations applied to the primary motor cortex (M1). The rMT will be measured in every child before each course of treatment. LF-rTMS (1 Hz) will be applied to the M1 for 20 min on the unaffected side. The stimulation intensity will be set at 90% rMT, with a total number of pulses of 1200 [39].

Routine rehabilitation consists of movement therapy and occupational therapy. The participants will receive 40 min of exercise training every day mainly on controlling the head, rolling over, sitting, crawling, standing, and walking. After movement therapy, participants will complete 20-minute occupational training tasks, mainly including upper limb function training, sensory integration therapy, and orthotics usage.

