#### Control group

The control group will receive the same routine rehabilitation regimen as the rTMS group, but a 20-minute sham stimulation will replace rTMS after routine rehabilitation therapy. A figure-eight advanced sham coil will be located on the unaffected side over the M1. The appearance, operation process, sound, and vibration sensation of the device during treatment will be the same as that during verum rTMS [40].

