## Discussion

This protocol aims to explore the safety and effects of VR therapy combined with rTMS on pain and motor development in children with spastic CP. Considering comfort and the possibility of visual impairment in children with CP, we chose immersive VR training in this protocol, which is easier for physiotherapists to use than VR glasses or gamepads [49]. Kirton et al. [50] applied 1 Hz rTMS at 100% rMT for 20 min over the contralesional M1 for 8 days in children with hemiplegia. We chose a similar rTMS program since it resulted in significant motor improvement and was demonstrated to be safe and well tolerated.

The results of this protocol may reveal the additive effects of the combination of VR therapy and rTMS or the effects of rTMS only on pain management in spastic CP patients. Self-reported pain or observation of pain-related behaviours are the two main methods for pain assessment in spastic CP patients due to their potential impairments in cognition and verbal expression. Self-reported pain assessments are strongly recommended by guidelines for measuring the severity of pain, but it may not be reliable if the participants have cognitive deficits [51]. Tools for pain assessment, such as the FLACC, are widely used in individuals with cognitive or intellectual impairment [52]. The design of the FLACC was based on 89 postoperative children in the post-anaesthesia care unit aged 2 months to 7 years, and it was developed to evaluate pain in children who cannot express pain in words [53]. A previous study showed that the FLACC pain score was valid (Pearson’s correlation coefficients of 0.76 and 0.59 with the observational visual analogue scale score) and reliable (Cronbach’s alpha > 0.9) for assessing pain in children with CP; however, this study demonstrated insufficient validity in adult patients [54, 55].

In addition to the assessment of pain and motor development, we plan to utilize balance, activity of daily living, and quality of life assessments, which may reflect the possibility of these children to return to family and school. This study protocol may further bridge the gaps among pain, motor development, and functional independence, and the results may reveal the impact of pain on returning to society in children with CP.

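### The inclusion list admits any spastic CP, contradicting the abstract's unilateral population and an rTMS/sham target defined only for children with an unaffected side

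*Protocol article*

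**What the plan says.** The protocol article describes the population in two ways.

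- **Abstract, Methods:** "We will recruit children aged 3–10 years with unilateral spastic CP (Gross Motor Function Classification System level I or II". The abstract's Purpose paragraph also names unilateral disease.
- **Inclusion criteria:** "①Diagnosis of spastic CP,②Aged 3 to 10 years,③GMFCS level I or II", followed by a history of pain. Laterality is not mentioned.
- **Exclusion criteria:** four items (brain trauma or surgery, recent CP treatment, rTMS contraindications, inability to cooperate with VR). None concerns bilateral disease.
- **Title and Introduction:** spastic CP without qualification. The aim is stated as "improving the pain and motor development of children with spastic CP".

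The intervention text depends on laterality.

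- **VR + rTMS group:** "LF-rTMS (1 Hz) will be applied to the M1 for 20 min on the unaffected side". The rTMS group section says that its stimulation is the same.
- **Control group:** "A figure-eight advanced sham coil will be located on the unaffected side over the M1".
- **Discussion:** the programme chosen as a model was given "for 20 min over the contralesional M1 for 8 days in children with hemiplegia".

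**The concern.** Sites enrol from the inclusion and exclusion lists, not from the abstract. Under those lists a child with bilateral spastic CP at GMFCS I or II and a history of pain is eligible. For that child the coil position is undefined in all three arms, because active and sham stimulation are both specified by reference to an unaffected side.

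Two things are at stake. First, the sample could differ from the population that the abstract names, so it would be unclear to whom the result applies. Second, the rTMS versus control contrast could average the intervention as specified with some other, unspecified placement. If bilateral children respond less to rTMS, the mean difference shrinks towards zero and power falls.

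**Working it through.** **1. The sections side by side**

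| Section | What it implies about laterality |
|---|---|
| Abstract (Purpose, Methods) | unilateral only |
| Title, Introduction (aim) | spastic CP, unspecified |
| Inclusion criteria | spastic CP, unspecified |
| Exclusion criteria | bilateral disease not removed |
| VR + rTMS, rTMS and Control groups | an unaffected side must exist |
| Discussion (rTMS precedent) | hemiplegia, contralesional M1 |

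The eligibility lists are wider than both the abstract and the intervention definition.

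**2. Inputs for an illustration of size**

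From Sample size: d = 0.9, α = 0.025, β = 0.1, 15% dropout. The sidedness of α is not stated; I take it as two-sided. The enrolment figure is 49 per group (147) in Sample size but 36 per group (108) in Ethics, so both are carried. Evaluable per arm, rounded down: 36 × 0.85 = 30.6, so 30; 49 × 0.85 = 41.65, so 41.

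**3. The plan's own figure**

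Normal formula: n = 2(2.2414 + 1.2816)²/0.9² = 2 × 12.41/0.81 = 30.6, so 31 per arm. Then 31 × 1.15 = 35.65, so 36 per arm and 108 in total. The exact t-test gives 32 per arm; 32/0.85 = 37.6, so 38 per arm and 114 in total. The figure of 147 is not reproduced from the stated inputs. That is a separate matter and is not relied on here.

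**4. Dilution of rTMS versus control**

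Assumptions, none of them in the document: a share p of children is bilateral; the effect is 0.9 in unilateral children and 0.9e in bilateral children; the within-subgroup SD is 1; control children do not differ by laterality.

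- Mean difference: δ = 0.9[1 − p(1 − e)]
- Extra variance in the rTMS arm: p(1 − p)[0.9(1 − e)]², half of which enters the average of the two arms' variances
- Diluted effect: d* = δ / √(1 + p(1 − p)[0.9(1 − e)]²/2)

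Example, p = 0.3 and e = 0: δ = 0.63; variance 1 + 0.21 × 0.81/2 = 1.085; d* = 0.63/1.042 = 0.605.

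Example, p = 0.3 and e = 0.5: δ = 0.765; variance 1 + 0.21 × 0.2025/2 = 1.021; d* = 0.765/1.011 = 0.757.

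Power, two-sample t-test, two-sided α = 0.025:

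| Bilateral share p | 30 per arm, no effect | 30 per arm, half effect | 41 per arm, no effect | 41 per arm, half effect |
|---|---|---|---|---|
| 0 | 88% | 88% | 96% | 96% |
| 20% | 66% | 79% | 81% | 91% |
| 30% | 52% | 73% | 68% | 87% |
| 40% | 39% | 68% | 52% | 82% |

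If the extra variance is ignored and only the mean is diluted, the no-effect figures at 20%, 30% and 40% are 69%, 56% and 42% with 30 per arm, and 83%, 71% and 57% with 41 per arm. The pattern is the same.

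**5. VR + rTMS versus rTMS**

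Let rTMS add r_U in unilateral and r_B in bilateral children, and let VR add v in both. The contrast is (r_U + v) − r_U = v in one subgroup and (r_B + v) − r_B = v in the other. The mean difference is v whatever p is, so a lost rTMS benefit cancels. Mixed response to rTMS could still widen the spread in both arms: with p = 0.3, e = 0 and v = 0.9, the standardised effect would be 0.9/√(1 + 0.21 × 0.81) = 0.83. That is a modest loss of precision, not a diluted effect.

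**The case against.** The strongest case on the other side is that this is an adjective dropped in a condensed article. The abstract is explicit, and stimulation cannot be delivered as written to a child with no unaffected side, so staff might never randomise one. Whether any would be enrolled is indeed unknown. The article nevertheless prints its eligibility criteria as a complete list, and that list conflicts with its own abstract. This is a contradiction, not detail left to a longer document.

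Four stronger readings are tempting, and the text does not support them.

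- **Both comparisons are diluted.** The rTMS group section makes rTMS identical in the two active arms. The VR contrast would be diluted only if VR worked through synergy with rTMS, which the Introduction calls unknown, or worked less well in bilateral children, which nothing in the document suggests.
- **Bilateral children get no benefit.** The primary outcome is pain. The hemiplegia study is cited for motor improvement, and the pain rationale in the Introduction draws on conditions such as fibromyalgia and postherpetic neuralgia, where the side of a brain lesion plays no stated part. Zero effect is a worst case.
- **The cited safety evidence leaves out part of the sample.** Only the precedent in the Discussion is tied to hemiplegia. The Introduction and Discussion also cite paediatric rTMS safety that is not visibly restricted in this way.
- **The trial's population is plainly unilateral.** The word occurs only in the abstract; the title and the stated aim say spastic CP.

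**Conclusion.** The point holds as an internal contradiction that must be resolved. The inclusion and exclusion lists admit children for whom the active or sham site is undefined, against the abstract's recruitment statement and outside the hemiplegia precedent. This conclusion rests on the text alone.

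The statistical consequence is conditional and concerns rTMS versus control only. Across assumed bilateral shares of 20% to 40%, power lies between 39% and 79% with 30 evaluable per arm (88% with no bilateral children) and between 52% and 91% with 41 per arm (96%). These figures rest on an assumed share, an assumed zero or half effect, and α read as two-sided. They show what could be lost and are no forecast. The need to fix the wording does not depend on them.

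**What to change.** Amend the protocol so that the abstract, the inclusion criteria and the active and sham stimulation sections describe the same children. The smallest edit consistent with the abstract, the stimulation target and the cited precedent is to insert *unilateral* in inclusion criterion 1, confirmed from the paediatrician's diagnosis that is already required. If the sponsor intends the wider population, the abstract and the definition of the stimulation site need to change instead. That is a clinical decision for the sponsor, on which this review takes no position.

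Keep any bilateral child already randomised in the intention-to-treat set, and report the two primary comparisons again in unilateral children as a sensitivity analysis. This needs laterality to be recorded at baseline; the article's list of baseline data does not name it.

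The cost is one word, an amendment and at most one field on the case report form, with no new procedure. The planned sample size does not change, because no input to it changes. The downside is a somewhat smaller recruitment pool, which is the pool the abstract already states.

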#### Exclusion criteria

①A history of brain trauma or brain surgery;②Received any drugs, surgery, or rehabilitation training to improve CP symptoms in the past 6 months;③Contraindications for rTMS, including cochlear or intracranial implants, elevated intracranial pressure, intracranial infection, and acute haemorrhagic diseases;④Inability to cooperate with VR treatment due to severe cognitive, visual, or hearing impairment.

### Random assignment and blinding

Random assignment will be performed based on the patient number and a random number sequence. The physiatrist in charge of patient recruitment will number patients according to the registration order. An independent researcher will generate a random number sequence (random seed: 16,264) through a website (www.randomization.com) and seal the allocation result in 108 sequentially numbered envelopes. Chief physiotherapists for the intervention will individually obtain the random allocation results to confirm the interventions. We will prepare a case report form for each participant to record evaluation results. Outcome measurements will be collected at baseline and after the intervention in a specialized venue by one experienced physician trained in basic and advanced courses for paediatric functional assessment. This assessor will be employed full time and will not participate in the design and group allocation of this study and will be unaware of the study objectives and the group allocation of patients; this assessor will not have access to the random allocation sequence. Moreover, he or she will be blinded during the entire process (including blinded to patient names, outpatient numbers, and other important information related to the identity of the patients) and will not be able to obtain relevant information on group allocation and intervention methods.

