### Sample size

G*Power 3.1 software was used to calculate the sample size. Based on Sahin [37] et al., the effect size was set to 0.9, with α = 0.025 and β = 0.1. Two sets of comparisons will be conducted (the VR + rTMS group vs. the rTMS group and the rTMS group vs. the control group). Considering a potential dropout rate of 15%, a total of 147 children (49 in each group) will be enrolled in this study.

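### The published seed and generator make the allocation list potentially reproducible, and the telephone, envelope and list-length texts need to be aligned

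*Protocol article*

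**What the plan says.** The section on random assignment and blinding names the generator and its seed: "An independent researcher will generate a random number sequence (random seed: 16,264) through a website (www.randomization.com". The same researcher is to "seal the allocation result in 108 sequentially numbered envelopes". List position follows from enrolment order: "The physiatrist in charge of patient recruitment will number patients according to the registration order". The results then go to the treating staff: "Chief physiotherapists for the intervention will individually obtain the random allocation results to confirm the interventions". The study design section supplies the ratio: "Participants will be randomly and equally divided into 3 groups".

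The section on study population and recruitment describes the release of the allocation differently: "After enrolment, an independent researcher will implement random assignment by telephone to avoid predictability".

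The list length of 108 agrees with the ethics section (108 children, 36 per group). The sample size section enrols 147 (49 per group).

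**The concern.** The stated purpose of the telephone step is to keep the next assignment unpredictable. Publishing the seed and the generator works against that purpose, because together they are the main secret input to the list. The article adds the list length, the number of equal groups and the rule linking a child to a list position.

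This matters more here than in a fully blinded trial. Only the evaluator is described as blinded, the discussion concedes that blinding the physiotherapists may be difficult, and the primary outcome is an observer-rated pain score. Concealment at enrolment therefore carries much of the protection against bias. If a recruiter could foresee the next arm, the choice or order of children enrolled could depend on it, and no analysis can reliably undo that.

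A second matter is that a reader cannot tell from the text who holds the envelopes, who opens them, or how the telephone step relates to them.

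**Working it through.** The article states no figure for predictability, so there is none to reproduce. The check asks how much remains secret, and then compares the texts.

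**1. What is printed and what is not.** Printed: seed 16,264, the website, 108 list positions, three equal groups, numbering by registration order. Not printed: whether blocks are used and of what size, which label stands for which arm, and how the website uses the seed.

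**2. How many lists fit.** Assume one fixed block size that is a multiple of 3 and divides the list length, and a website that turns a given seed and settings into one fixed sequence.
- 108 = 2² × 3³, so the possible block sizes are 3, 6, 9, 12, 18, 27, 36, 54 and 108: 9 options.
- Three labels can be ordered in 3! = 6 ways.
- Candidate lists: 9 × 6 = 54.
- If the list were made for 147 = 3 × 7², the block sizes are 3, 21 and 147, and the candidates are 3 × 6 = 18.

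**3. How many known allocations would be needed.** Each known allocation distinguishes at most three outcomes, so the minimum is log(candidates) / log 3.
- 54 lists: log 54 / log 3 = 3.6, so at least 4.
- 18 lists: log 18 / log 3 = 2.6, so at least 3.

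These are lower bounds. More are needed where candidate lists agree in their early positions, and more again if block sizes vary.

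**4. Who has that information.** The chief physiotherapists obtain each allocation and so know past arms. The recruiting physiatrist controls the numbering, but the article does not say that this person learns past arms. Prediction at enrolment would therefore take deliberate reconstruction and shared information. Without it, the chance of guessing the next arm is about 1/3. With the right list identified, it would approach 1.

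**5. Which children are exposed.** The protocol version is dated 28 February 2023, registration 28 March 2023, and the article 26 September 2023. Recruitment is written in the future tense, but no number randomised by publication is given. Only allocations made after publication could be predicted from the article.

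**6. Telephone and envelopes side by side.** One section has an independent researcher assigning by telephone after enrolment. The other has an independent researcher sealing envelopes and physiotherapists obtaining results. A researcher who keeps the envelopes, opens the next one and telephones the result would satisfy both. The texts are unreconciled, not contradictory.

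**7. List length.** 147 − 108 = 39 children would have no envelope if 147 is the total. The stated inputs are "the effect size was set to 0.9, with α = 0.025 and β = 0.1", with 15% dropout. Taking α as two-sided (the article does not say), the normal approximation gives 31 per arm and the exact t calculation 32.
- 31 × 1.15 = 35.7, so 36 per arm (108 in total).
- 32 / 0.85 = 37.6, so 38 per arm (114 in total).

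The other variants tried (α of 0.05, 0.025 or 0.0125, one- or two-sided, power 0.80 or 0.90, rank-test inflation) reached at most 46 per arm. None gave 49.

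**The case against.** The strongest reply is that reproduction of the list has not been shown. Block size, label order and the website's handling of the seed are all unstated, and the list length is itself disputed between 108 and 147. That stands, and it rules out the reading that anyone can now read off the next child's arm with near certainty. It also rules out the reading that every planned allocation is affected, since those made before publication could not be predicted from the article.

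A reader might also infer that assessor blinding is broken. The documents do not support this. The assessor takes no part in allocation, has no access to the sequence, and is kept from patient names, outpatient numbers and other identifying information. A regenerated list is of little use to someone who cannot link a child to a list position.

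A reader might infer that only one of the two release routes can be the real one, or that the telephone is the better. Neither follows: the routes can be combined, and properly held sealed envelopes can also conceal. Consent before randomisation and assignment after enrolment are already stated.

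What remains is that concealment should not rest on nobody trying to recover a few settings, and that the procedure is described in two pieces that are not joined.

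**Conclusion.** The point holds as a weakening of allocation concealment, not as its loss. Under the assumptions of one fixed block size and a seed that determines the sequence, about 54 candidate lists remain (18 if the list has 147 places), and at least four known allocations (three for 147) would be needed to identify the right one. The exposure is confined to children randomised after 26 September 2023, whose number the article does not give. The telephone and envelope descriptions are compatible but leave custody and opening of the envelopes undefined. The list of 108 agrees with the ethics section and falls 39 short of the sample size section.

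**What to change.** - For all children not yet randomised, generate a new sequence with an undisclosed seed and undisclosed settings, held only by the independent researcher. Keep the seed out of public text from now on. Deleting it from the published article alone would restore nothing.
- If randomisation is already complete, report the disclosure as a limitation.
- Rewrite the recruitment section and the section on random assignment and blinding as one procedure: who holds the envelopes, who opens them and when, and how the result reaches the treating physiotherapist. Telephone and envelopes may be combined.
- Reconcile 108 and 147, and make the list length equal to the agreed total.

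The cost is one new list, a new set of envelopes if they are kept, and a short amendment. Replacing the list needs no additional children, visits or outcome measurements. If 147 proves to be the total, 39 further allocations have to be generated in any case.
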